### Statistical analysis

2.11

All analyses will be performed using SPSS version 27.0, and figures will be generated using GraphPad Prism version 10. The primary analysis will follow the intention-to-treat principle, with per-protocol analysis conducted as sensitivity analysis. Safety analysis will include all participants who receive at least one treatment session. Baseline characteristics will be summarized by group using appropriate descriptive statistics. Continuous variables will be presented as mean ± standard deviation or median with interquartile range, as appropriate, and categorical variables as frequencies and percentages. Baseline comparability between groups will be assessed descriptively and, where appropriate, using *t*-test or Mann–Whitney *U*-test for continuous variables and chi-square test or Fisher's exact test for categorical variables. The primary outcome, overall clinical response rate at week 4, will be compared between groups using logistic regression, with results reported as odds ratios and 95% confidence intervals. Repeated continuous secondary outcomes will be analysed using mixed-effects models, including group, time, and group-by-time interaction. Categorical secondary outcomes will be analysed using chi-square test or Fisher's exact test, as appropriate. Missing primary outcome data will be handled by multiple imputation when the proportion of missing data is non-negligible and the missing-at-random assumption is considered reasonable. Complete-case analysis and per-protocol analysis will be conducted as sensitivity analyses to evaluate the robustness of the primary findings. As this is an exploratory pilot trial, secondary outcome analyses will be considered exploratory. All tests will be two-sided, with *P* < 0.05 considered statistically significant.

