### Study design

2.1

This is a prospective, single-center, parallel-group, randomized, sham-controlled exploratory trial. The protocol was prepared in accordance with the SPIRIT 2025 statement (22), with the corresponding checklist provided in Supplementary Table S1, and the acupuncture intervention is reported with reference to the revised STRICTA recommendations (23), as detailed in Supplementary Table S2. Sixty eligible participants will be randomly assigned in a 1:1 ratio to the acupuncture group or the sham acupuncture group.

Each participant will be followed for 8 weeks, including baseline assessment within 24 h after enrollment, 4 weeks of treatment, and 4 weeks of post-treatment follow-up. The primary objective is to evaluate the efficacy and safety of acupuncture as an adjunct to conventional therapy for INOCA-related CMVD and to explore its potential effects on angina-related health status, quality of life, endothelial function, and inflammation-related biomarkers.

This study protocol is version 1.0. It has been approved by the Ethics Committee of Guang'anmen Hospital, China Academy of Chinese Medical Sciences, and was registered with the International Traditional Medicine Clinical Trial Registry on March 13, 2026 (registration number: ITMCTR2026000515). The trial will be conducted in accordance with the Declaration of Helsinki. Eligible participants will be enrolled voluntarily and will provide written informed consent before any study-specific procedure. The study flowchart and the schedule of enrollment, interventions, and assessments are shown in Figure 1 and Table 1.

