#### Secondary outcomes

2.8.2

1.Seattle Angina Questionnaire (SAQ) scores:

The SAQ-SS and individual SAQ domain scores will be assessed at baseline, week 4, and week 8 to evaluate continuous changes in angina-related symptoms and health status.
2.Angina attack frequency:Angina episodes will be continuously recorded and evaluated using an angina diary from baseline through the end of the 8-week follow-up period. The diary will document the onset time, end time, duration of each episode, pain intensity measured by the visual analogue scale (VAS), accompanying symptoms, medication use, nitroglycerin dosage, and symptom relief.
3.EuroQol five-dimension five-level questionnaire (EQ-5D-5L):The EQ-5D-5L will be assessed at baseline, week 4, and week 8. This instrument includes five dimensions: mobility, self-care, usual activities, pain/discomfort, and anxiety/depression, each rated on a five-level scale (29). In addition, the EQ visual analogue scale (EQ-VAS) will be recorded to reflect the participant's self-rated health status on the day of assessment. The EQ-5D-5L will be used to evaluate the impact of acupuncture on overall health status and quality of life.
4.Traditional Chinese medicine (TCM) syndrome score:The TCM syndrome score will be assessed at baseline, week 4, and week 8. The scoring system includes the following major symptoms: chest pain and chest tightness, each scored as 0, 2, 4, or 6 points; and the following minor symptoms: palpitations, shortness of breath, fatigue, spontaneous sweating, and dark complexion, each scored as 0, 1, 2, or 3 points. Tongue manifestation, tongue coating, and pulse condition will each be scored as 0 or 1 point. A higher total score indicates more severe manifestations of qi deficiency and blood stasis syndrome. The total TCM syndrome score and its change from baseline will be compared between the two groups to evaluate the effect of acupuncture on qi deficiency and blood stasis syndrome.

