5.Endothelial function and inflammation-related biomarkers:Blood samples will be collected at baseline and week 4 for measurement of nitric oxide (NO), endothelin-1 (ET-1), and high-sensitivity C-reactive protein (hs-CRP). These markers will be used to reflect changes in endothelial vasomotor function and inflammatory status and to explore the potential biological effects of acupuncture in CMVD (30, 31). These biomarkers are intended to explore short-term treatment-related changes in endothelial function and inflammatory status during the intervention period.

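### The mixed models for repeated continuous secondary outcomes list no baseline adjustment, so the week-4 comparison is less precise than the collected data allow

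*Protocol article*

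**What the plan says.** Section 2.11 (Statistical analysis) gives the model for this class of outcome: "Repeated continuous secondary outcomes will be analysed using mixed-effects models, including group, time, and group-by-time interaction". The stated terms include no baseline covariate and no restriction on the baseline means.

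The measurement times are in Section 2.8.2 and Table 1:

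- **SAQ:** "The SAQ-SS and individual SAQ domain scores will be assessed at baseline, week 4, and week 8". EQ-5D-5L and the TCM syndrome score follow the same three visits. For the TCM score, Section 2.8.2 also announces a between-group comparison of change from baseline.
- **NO, ET-1 and hs-CRP:** "Blood samples will be collected at baseline and week 4 for measurement of nitric oxide", with no week-8 sample. The Discussion repeats this as a limitation.

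On the design, Section 2.1 states: "Sixty eligible participants will be randomly assigned in a 1:1 ratio". Section 2.6 specifies simple randomization, declines stratification by baseline SAQ score, and has baseline assessment completed before the envelope is opened. Section 2.10 bases the size on 25 participants per group, recruits 30 to allow for dropout, and says the pilot should yield preliminary effect-size estimates, naming SAQ-SS change and the week-4 responder rate. Section 2.11 declares the secondary analyses exploratory.

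**The concern.** In a randomized trial the two arms have the same expected baseline mean. A model in which baseline is one of the time points, and which also has a group main effect, does not use this fact. It estimates the baseline difference from the data and subtracts it in full from the week-4 difference. When baseline and follow-up are only moderately correlated, subtracting the whole difference over-corrects and adds noise. A baseline-adjusted analysis subtracts only the share that the correlation supports.

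Two features of this trial make the point worth raising. Simple randomization without stratification leaves chance baseline differences to the analysis: with 30 per arm, the standard deviation of the difference in baseline means is sqrt(2/30) = 0.26 SD. And the effect estimate for continuous SAQ-SS change, which Section 2.10 names among the pilot's purposes, comes from this model. A wider interval than necessary makes it a weaker guide to the confirmatory trial.

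**Working it through.** **Which reading of time applies.** With samples at baseline and week 4 only, a model of post-baseline values has a single time point, hence no time factor and no interaction. So for NO, ET-1 and hs-CRP the stated terms work only if baseline is a level of time. For the three-visit outcomes the article does not say so outright, but it is the natural reading of repeated outcomes measured from baseline onwards.

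**Inputs.** From the document: 1:1 allocation and 25 evaluable per arm (Section 2.10; 25 × 1.20 = 30 recruited per arm, 60 in total, as stated). The plan gives no precision or power figure for secondary outcomes, so there is none to reproduce. Assumed: rho from 0.3 to 0.8, equal variance s² at baseline and week 4, complete data, and, for three visits, the same correlation between all pairs of visits.

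**Formulas**, with n per arm:

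- Stated model, free baseline means: Var = 2(1 − rho)s² × 2/n, the change-score variance.
- Common or adjusted baseline: Var = (1 − rho²)s² × 2/n.
- Ratio: 2(1 − rho)/(1 − rho²) = 2/(1 + rho), which does not depend on n.

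Example at rho = 0.5 and n = 25, in units of s²: stated model 2 × 0.5 × 0.08 = 0.080, SE 0.283; adjusted 0.75 × 0.08 = 0.060, SE 0.245; ratio 1.33.

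| Assumed rho | SE, stated model (SD units) | SE, baseline-adjusted | Variance ratio | Variance saved | Power at an assumed 0.5 SD effect |
|---|---|---|---|---|---|
| 0.3 | 0.335 | 0.270 | 1.54 | 35% | 32% → 46% |
| 0.5 | 0.283 | 0.245 | 1.33 | 25% | 42% → 53% |
| 0.7 | 0.219 | 0.202 | 1.18 | 15% | 63% → 70% |
| 0.8 | 0.179 | 0.170 | 1.11 | 10% | 80% → 84% |

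Power is two-sided at 0.05 with 25 per arm. The 0.5 SD effect is for illustration only; the document gives no effect size or SD.

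**Check with three visits.** Exact generalized least squares for baseline, week 4 and week 8 gave a week-4 contrast SE of 0.3347, 0.2828 and 0.2191 with free baseline means at rho 0.3, 0.5 and 0.7. These match the change-score formula to four decimals. With baseline means constrained equal the SEs were 0.2698, 0.2449 and 0.2020. The variance ratios were 0.65, 0.75 and 0.85, that is (1 + rho)/2.

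**In participants.** To match the adjusted analysis, the stated model would need 25 × 1.54 = 38.5, 25 × 1.33 = 33.3 or 25 × 1.18 = 29.5 per arm at rho 0.3, 0.5 and 0.7.

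**Against ignoring baseline.** Comparing week-4 values alone has SE sqrt(2/25) = 0.283. At rho 0.5 the stated model equals this. Below 0.5 it is worse than not using baseline at all.

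**Two limits on the formula.** If the SDs at baseline (s0) and week 4 (s1) differ, the change-score variance exceeds the adjusted one by a factor proportional to (s0 − rho × s1)², which is never negative, so the direction holds. Estimating the baseline slope costs a factor of about 1 + 1/(2n − 4) = 1 + 1/46 = 1.02 at n = 25, which is small against the ratios above.

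**The case against.** The strongest reply is that the free-baseline model is valid, unbiased and widely used, that the secondary analyses are declared exploratory, and that an article may leave baseline handling to an analysis plan not shown here. The first two points stand and limit the weight of this one. The third stands only in part. The article does not merely stay silent: it lists the model terms, and for the biomarkers those terms leave no workable reading other than a free baseline mean in each arm. For the three-visit outcomes the list might not be exhaustive, so there the point rests on the natural reading.

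Two further replies are fair. The identity with a change-score comparison is exact only with complete data; with the anticipated dropout of about 20%, a likelihood-based model also uses participants who have a baseline value only. And the SD of SAQ-SS change can be estimated equally well either way, so what suffers is the precision of the effect estimate, not the pilot's estimate of variability.

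A reader might be tempted to go further in three ways that the document does not support:

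- **All outcomes forced into one normal model.** Section 2.11 speaks of models in the plural, limits them to continuous outcomes, and names no distribution, link or scale. It does not say that angina attack counts are treated as continuous or that biomarkers are analysed untransformed. The count model and the biomarker scale are details for the analysis plan and are not part of this point.
- **The result will be an overall interaction test with two degrees of freedom.** The article does not say so, and the week-4 contrast is a parameter of the same model.
- **False-positive results or bias.** Nothing here implies either.

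**Conclusion.** The point holds as a loss of precision. On the stated terms, with baseline as a level of time, the week-4 contrast has 1.54, 1.33 or 1.18 times the variance of a baseline-adjusted analysis at assumed correlations of 0.3, 0.5 and 0.7. Equivalently, 35%, 25% or 15% of the variance could be saved, falling to 10% at 0.8. The direction does not depend on the exact correlation within this range; the size does, and the document does not give the correlation. The figures also assume equal variances and complete data.

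The consequence is modest: wider intervals in exploratory analyses, with the primary logistic regression unaffected. It is still worth acting on, because the better method uses values already collected and serves the SAQ-SS effect estimate that Section 2.10 wants from this pilot.

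**What to change.** Add one statement on baseline handling to Section 2.11 or the analysis plan, choosing one of two forms:

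- **Constrained baseline (cLDA).** Keep baseline as a response, but let both arms share one baseline mean and allow arm differences only at week 4 and, where measured, week 8. In practice the treatment indicator is set to zero at baseline for everyone.
- **Baseline as covariate.** Model post-baseline values only, adjusted for the participant's baseline value. For NO, ET-1 and hs-CRP this is a single analysis of covariance at week 4.

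In either form, name the week-4 between-arm contrast with its 95% confidence interval as the reported estimate.

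The cost is a sentence of text and a change of model terms. No participants, visits or measurements are added. Baseline values should be available for everyone randomized, since Section 2.6 requires baseline assessment before the envelope is opened. The primary analysis and the sample size need no change on this account.

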#### Additional outcomes

2.8.3

Additional outcomes in this study will include baseline expectancy assessment, credibility assessment of acupuncture therapy, the Clinical Global Impression–Improvement scale (CGI-I), and participant blinding assessment.

Baseline expectancy will be assessed before the first treatment session. Credibility of acupuncture will be evaluated at baseline and again at week 4 (32). The CGI-I will be assessed at week 4 and at the end of follow-up to capture participants' global perception of change relative to baseline (33). Participant blinding assessment will be completed within 5 min after the final treatment session at week 4. Participants will be asked to guess whether they received true acupuncture, sham acupuncture, or were unsure. The success of blinding will be evaluated by comparing the distribution of allocation guesses between groups (34).

Because objective evidence of myocardial ischemia is required for inclusion, this study focuses on INOCA-related CMVD rather than broader ANOCA or asymptomatic coronary microvascular dysfunction. Accordingly, the symptom- and quality-of-life-related outcomes, including SAQ scores, angina attack frequency, EQ-5D-5L, and CGI-I, will be evaluated in a symptomatic INOCA-related CMVD population.

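### Five-level EQ-5D-5L dimensions, if compared between groups, would fall by inference under a chi-square or Fisher rule that ignores order and baseline and gives no directional estimate

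*Protocol article*

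**What the plan says.** Protocol article, section 2.11 (Statistical analysis), sets two rules for secondary outcomes. The first is: "Repeated continuous secondary outcomes will be analysed using mixed-effects models, including group, time, and group-by-time interaction". The second is that "Categorical secondary outcomes will be analysed using chi-square test or" Fisher's exact test, whichever suits. The section does not say which outcomes count as categorical. Mann-Whitney appears only for baseline comparison of continuous variables. The section also states that "secondary outcome analyses will be considered exploratory", and: "All tests will be two-sided, with *P* < 0.05 considered statistically significant".

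Section 2.8.2 describes the EQ-5D-5L as five dimensions, "each rated on a five-level scale", plus the EQ-VAS, which "will be recorded to reflect the participant's self-rated health status on the day of assessment". On timing: "The EQ-5D-5L will be assessed at baseline, week 4, and week 8". It does not say whether dimension levels, an index value or only the EQ-VAS will be compared between groups.

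Section 2.10 sets 25 participants per group as the target and 30 per group for recruitment. It gives preliminary effect-size information as one purpose of that number.

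**The concern.** The chi-square/Fisher sentence is a stated rule, so the question is what it governs. Of the five secondary outcomes in section 2.8.2, the SAQ scores, the TCM total score and the biomarkers are numeric, and angina attack frequency is a count. Only the EQ-5D-5L dimensions are clearly categorical. Either the rule governs them or it governs none of the listed secondary outcomes.

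Applied to a table of two groups by five levels, the rule has three weaknesses:

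- It ignores order. A shift of one level counts the same as a shift of four, and chi-square spends 4 degrees of freedom on a question about one direction.
- It cannot use the baseline level, although that level is collected.
- It gives a p-value without a direction or an effect size. The primary outcome, by contrast, gets an odds ratio with a 95% CI.

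At stake is how much an exploratory pilot of this size can learn from these items. The primary analysis is not affected.

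**Working it through.** **Plan's own figures.** The document states no power for any outcome. The sample size reproduces as 25 × 1.20 = 30 per group, 60 in total. The check below uses 25 per group.

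**Inputs from the document.** 1:1 allocation, two-sided 0.05, five levels, 25 per group.

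**Assumptions, because the document gives none.** The level distributions, and a common odds ratio (OR) as the form of the effect.

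**Step 1: cost of the extra degrees of freedom.** Give both tests the same noncentrality λ. The critical values are 3.84 (1 df) and 9.49 (4 df). Where the 1-df test has 80% power, λ = 7.85, and the 4-df test then has 60% power. For 80% power the 4-df test needs λ = 11.94, so the sample-size ratio is 11.94 / 7.85 = 1.52, an efficiency loss of 1 − 1/1.52 = 34%. At other levels of 1-df power:

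| Power, 1 df | Power, 4 df | Relative loss |
|---|---|---|
| 30% | 18% | 41% |
| 50% | 31% | 38% |
| 70% | 48% | 31% |
| 90% | 74% | 18% |

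The relative loss shrinks as the effect grows.

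**Step 2: simulation at 25 per group.** There were 20,000 trials per scenario and four assumed five-level distributions: one even, one bell-shaped and two piled towards one end. The comparison is Pearson chi-square against the tie-corrected Mann-Whitney test, which is the score test of the unadjusted proportional-odds model. Relative loss = 1 − (chi-square power / Mann-Whitney power).

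| Common OR | Chi-square | Mann-Whitney | Relative loss |
|---|---|---|---|
| 2 | 12–15% | 24–27% | 44–52% |
| 3 | 27–34% | 49–57% | 40–45% |
| 4 | 41–53% | 66–75% | 30–38% |
| 5 | 53–66% | 77–87% | 24–32% |
| 6 | 61–76% | 84–92% | 17–27% |

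For example, at OR 6 with the even distribution the loss is 1 − 76.3/92.4 = 17%. The largest absolute gap is about 25 points (at OR 4 with the bell-shaped distribution, 75.3 − 50.0 = 25.3). With no effect, chi-square rejects in about 3.5 to 5% of trials and Mann-Whitney in about 5%. At 30 per group the relative loss is 43–51% at OR 2 and 12–21% at OR 6.

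A rerun with two fully specified starting distributions, (0.20, 0.30, 0.25, 0.15, 0.10) and (0.40, 0.30, 0.15, 0.10, 0.05), gave powers inside every range in the table. Its largest absolute gap was 69.3 − 42.6 = 26.7 points.

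**Step 3: is Fisher's test the likelier choice?** Take (0.40, 0.30, 0.15, 0.10, 0.05) and OR 3. The cumulative odds 0.667, 2.333, 5.667 and 19 become 2, 7, 17 and 57. The shifted distribution is therefore (0.667, 0.208, 0.069, 0.038, 0.017). Expected counts per cell, 25 × the mean of the two probabilities, are 13.3, 6.4, 2.7, 1.7 and 0.8. Six of the ten cells are below 5, so Fisher's test would often be the one used.

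**Step 4: Fisher's test (Freeman-Halton form), 25 per group.** There were 1,500 trials per scenario on three of the distributions. Power was 15–17% at OR 2, 34–36% at OR 3 and 48–55% at OR 4. Against Mann-Whitney the relative loss was about 33–43%, 31–39% and 26–28%.

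**The case against.** The strongest reply is that the plan never says the EQ-5D-5L dimensions will be tested by chi-square or Fisher. An index value or the EQ-VAS, measured at three visits, would go to the mixed model, and the article may leave that choice to a fuller document. This stands in part. A reader might infer that the plan commits the dimensions to these tests, but the text supports only the conditional statement. What remains is that the rule is stated, and the dimensions are the only listed secondary outcome it clearly fits.

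A reader might also extend the point to the CGI-I and to the three bands of SAQ-SS change. The documents do not support that. The CGI-I ("The CGI-I will be assessed at week 4 and at the end of follow-up") is an additional outcome in section 2.8.3, so the rule does not formally cover it. The bands appear only in the description of the primary outcome, and no between-group test of them is planned.

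A further reply is that the simulation favours the ordinal test, because a common odds ratio is the pattern that test is built for. That is fair, and it is why the result is given as a range under assumptions. No gain from baseline adjustment was simulated or counted.

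Finally, the analyses are exploratory, no power is claimed, and the sample size is aimed mainly at SAQ-SS change and the responder rate. Counts by level would also let a reader derive an unadjusted odds ratio. All of this stands, and it keeps the point small. It does not supply a baseline-adjusted estimate or an interval.

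**Conclusion.** The point holds in a limited, conditional form. If EQ-5D-5L dimension levels are compared between groups, the only stated rule that fits them ignores their order, discards the baseline level and produces no directional estimate.

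The relative power loss is roughly 20 to 50%, or about 25 percentage points at most. This assumes five levels, 25 per group, a common odds ratio of 2 to 6 and the assumed distributions.

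A reader might take 40 to 50% as the general cost, but that is not supported. It applies to odds ratios of about 2 to 3 with Pearson chi-square. The loss falls to 17–38% at odds ratios of 4 to 6, and with Fisher's test it is mostly below 40%. Nor does the choice of test explain all of the low power: at an odds ratio of 2 the ordinal test itself reaches only 24–27%.

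This is a worthwhile but low-priority improvement to exploratory analyses, and it does not threaten the primary result.

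**What to change.** Replace the sentence on categorical secondary outcomes in section 2.11 with text such as:

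> Ordered secondary outcomes (EQ-5D-5L dimension levels, if compared between groups) will be analysed by proportional-odds regression with the baseline level as covariate, reporting a common odds ratio with 95% CI. The Mann-Whitney test will be used where levels are sparse or proportional odds is doubtful. Chi-square or Fisher's exact test will be kept for binary or unordered variables.

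The same method can serve the CGI-I if it is compared between groups; that scale is rated relative to baseline, so it has no baseline level to adjust for. If only the EQ-VAS or an index value is to be compared, saying so in section 2.8.2 settles the matter and leaves those measures to the mixed model.

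The cost is one sentence. No new data or visits are needed, and the planned software can fit the model. The small downside is that the proportional-odds assumption must be checked and sparse levels may need to be collapsed.
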